### Supplies

This study will include the following supplies:

Meta Quest 3 ER head-mounted display with handheld controllers, preinstalled with several active video games that incorporate age-appropriate themes and music and mindfulness gaming. The Quest allows gameplay in both virtual and mixed reality. The Quest will come equipped with accessories to enhance accessibility and usability for children with disabilities, namely, an aftermarket head strap to reduce frontal pressure on the face and pressure on the neck, and hand straps to allow gameplay for children with minimal grip strength.Fitbit Flex 2 (Google) activity monitor and sleep tracker, which will be used to track daily steps.

### Intervention Procedures

In summary, key features of the intervention include (1) an ER exercise intervention that has been adapted for a variety of functional abilities and fitness levels; (2) theory-based behavioral telecoaching; and (3) brief mindfulness ER gaming.

### ER Intervention

IS participants will undergo an ER intervention that will last approximately 14 weeks in total. IS participants will start the ER intervention in the hospital, which will last approximately 6 weeks. They will then participate in an 8-week, home-based program with behavioral coaching. IS participants will be provided with a Quest headset within their hospital room to begin the intervention. In the hospital, IS participants will be prescribed to complete at least 15 minutes of exercise and 10 minutes of mindfulness gaming per day. Video games will be preinstalled on the headsets. Exercise games will include boxing, fitness games, and rhythmic movement-to-music games (eg, Beat Saber [Beat Games], Les Mills Body Combat [Odders], Synth Riders [Kluge Interactive], Creed: Rise to Glory [Survios]). Mindfulness gaming will include TRIPP (TRIPP, Inc.), which is a comprehensive, high-quality mindfulness ER experience that can be purchased in the digital Quest store. TRIPP includes an extensive archive of content with techniques related to breathing, meditation, yoga, pain distraction, and positive self-image. After hospital discharge, IS participants will be provided with a Quest headset and be prescribed to complete the same exercise prescription 3 times per week. The prescription will be gradually progressed through weekly behavioral coaching calls, with a goal of reaching 150 minutes of moderate-intensity ER exercise per week by the fifth week of the home intervention. The desired 150 minutes was chosen because it will likely exceed an exercise dose that could improve health in people with mobility disabilities who are physically deconditioned [52].

WC participants will receive the same intervention as those in the IS group. Participants will be given a Meta Quest 3 ER headset that will come preinstalled with the intervention games. However, WC participants will not receive the intervention until 8 weeks after hospital discharge. Thus, WC participants will be in the study for a total of approximately 22 weeks. The WC control group will undergo usual care for a total of 14 weeks (6-week hospital stay and 8-week wait period at home) before starting the 8-week intervention. Usual care consists of inpatient and outpatient rehabilitation.

### Home-Based Behavioral Coaching

The home-based intervention will include behavioral coaching through phone calls with both the child and caregiver. The behavioral coaching calls will aim to enhance adherence by providing a sense of accountability [47], basic exercise knowledge, gameplay tips to increase mastery, and gradually promoting walking or community activity as a supplement to video gameplay. The rationale for promoting community physical activity is to transform a patient into a participant in their community by ER gameplay in the early intervention period to improve fitness levels that support gradual reintegration into the community. Calls will last approximately 15 minutes and will be provided weekly. Caregivers will be included in the calls since caregiver knowledge and attitude are determinants of participation.

The coaching calls will include behavior change strategies framed within the Social Cognitive Theory [48], including goal setting, confidence building, setting reasonable expectations, and understanding benefits. These strategies have been found to enhance the likelihood of promoting exercise behavior among people with disabilities [49] and cancer survivors [50]. Social Cognitive Theory provides a targeted approach toward promoting exercise behavior through 4 constructs: self-efficacy (perceived control over one’s behaviors), outcome expectations, sociostructural factors (facilitators and barriers), and goals [48,51]. The coaching calls will be delivered by the lead interventionists (AW and BL).

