#### Aim 1 (Primary Outcome): Physical Activity

Physical activity level will be measured by steps per day using a Fitbit Flex 2 wrist-worn tri-axial accelerometer. The participants from both the IS and WC groups will be equipped with the Fitbit Flex as soon as they join the study. IS participants will wear the Fitbit Flex and daily steps will be measured until they complete the entire study (hospital phase, weeks 0-6; home intervention phase, weeks 7-14). WC participants will wear the Fitbit Flex, and daily steps will be measured until they complete all 3 phases that are assigned to their group: hospital phase, weeks 0-6; home wait period, weeks 7-14; and home intervention, weeks 15-22. The Fitbit Flex has evidence to support good-to-excellent validity and reliability for measuring step counts across a variety of populations, both general [53] and clinical [54], and moderate data to support validity for pediatric patients with cancer [55]. Additional rationales for the Fitbit Flex include ease of use, robust memory (30 days), water resistance, the small size of the monitor unit, and low cost. Although Actigraph GT3x monitors have more evidence to support their use among pediatric patients with cancer and are considered the gold standard [55], we chose not to use them due to their short storage capacity (42 days max) and an inability for both the participant and the telecoach to view and monitor their steps (app and web-based feedback; a critical component of coaching). Step counts are inversely associated with mortality [56], as well as fatigue and cumulative symptoms among patients with pediatric cancer [57].

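### In weeks 7-14 the step counter is also a coaching tool in the immediate-start arm only, so wear and syncing of the primary-outcome device could differ by arm

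*Protocol article*

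**What the plan says.** The Protocol article, under Aim 1 (Primary Outcome): Physical Activity, fixes the outcome and the device: "Physical activity level will be measured by steps per day using a Fitbit Flex 2 wrist-worn tri-axial accelerometer". Both arms have it from enrolment ("The participants from both the IS and WC groups will be equipped with the Fitbit Flex as soon as they join the study"), and the waitlist control (WC) arm keeps it throughout: "WC participants will wear the Fitbit Flex, and daily steps will be measured until they complete all 3 phases that are assigned to their group". Weeks 7-14 are the home intervention for the immediate-start (IS) arm and the home wait for WC.

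Coaching belongs to the home program. Under Home-Based Behavioral Coaching: "The home-based intervention will include behavioral coaching through phone calls with both the child and caregiver", and "Calls will last approximately 15 minutes and will be provided weekly". Under ER Intervention, WC does not start the program until 8 weeks after discharge, so its calls fall in weeks 15-22.

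The Aim 1 section explains why the research-grade monitor was not used. One reason is "an inability for both the participant and the telecoach to view and monitor their steps (app and web-based feedback; a critical component of coaching".

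Under Measures, the data collections compared between arms are at week 0, about week 3, about week 6, week 10 and week 14. All after the first are by phone or videoconference. Study Design and Overview says that data are gathered remotely over the whole study.

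**The concern.** Steps per day records wearing and syncing as well as walking. In the IS arm at home, a coach who can see the step record speaks to the child and caregiver every week. One stated aim of the calls is accountability. A device that is off the wrist, uncharged or not synced could come to light within about a week. A WC family wears the same device over the same weeks, and the article states no study contact between data collections about four weeks apart.

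Two kinds of error could follow. Unworn or partly worn days that enter the data as low counts would pull down the WC mean and favour IS. Days lost because the device was not synced would leave a selected set of WC days, and the direction of that error cannot be predicted. Blinding the outcome assessor does not help, because the mechanism is contact with the coach. Nor can the mixed model on all available measures tell a recorded low count from an unworn device. With 8 children per arm, a few poor wearers can move an arm mean.

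**Working it through.** The plan gives no step mean, SD, effect size or wear rate, so there is no figure of its own to reproduce here. The check uses the schedule and the stated device memory, then an illustration on assumed inputs.

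**1. Schedule.** IS: 6 + 8 = 14 weeks. WC: 6 + 8 + 8 = 22 weeks. Both agree with the article.

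**2. Stated contacts in weeks 7-14.**

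| | Weekly calls | Data collections | Total | Longest planned gap |
|---|---|---|---|---|
| IS | 8 (one per week for 8 weeks) | 2 (weeks 10 and 14) | 10 | 7 days |
| WC | 0 | 2 (weeks 10 and 14) | 2 | 28 days |

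The 28 days are (10 − 6) × 7 and (14 − 10) × 7.

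**3. Gap against memory.** The stated memory is 30 days. Days lost = max(0, gap − 30), assuming that data leave the device only at a study contact. The article does not say this.

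- Planned WC gap: 28 − 30 < 0, so 0 days are lost, with 30 − 28 = 2 days to spare.
- WC collection 7 days late: 35 − 30 = 5 days lost, 5/35 = 14%.
- Week 10 collection missed: 56 − 30 = 26 days lost, 26/56 = 46%.
- IS: at least four successive calls would have to be missed (gap 5 × 7 = 35 days) before any loss.

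On schedule nothing is lost in either arm. The arms differ in how much slippage they tolerate.

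**4. Wear illustration (all inputs assumed).** Suppose that true activity is equal, that worn days average 4000 steps in both arms, and that unworn days are kept and read as zero. The false IS advantage is then wear difference × 4000:

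- 10 percentage points: 0.10 × 4000 = 400 steps/day
- 20 percentage points: 0.20 × 4000 = 800 steps/day
- 30 percentage points: 0.30 × 4000 = 1200 steps/day

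As a ratio, which does not depend on the 4000, the apparent IS excess is (IS wear ÷ WC wear) − 1. With IS wear at 95%, WC wear of 95%, 85%, 75% or 60% gives 0%, 12%, 27% or 58%.

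For the small sample: if two of eight WC children wear the device half the time, the WC mean falls by (2/8) × 0.5 × 4000 = 500 steps/day. If unworn days are set to missing instead, none of these figures applies.

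**5. Storage rationale.** The same section credits the chosen device with "ease of use, robust memory (30 days), water resistance" and rejects the other monitors "due to their short storage capacity (42 days max"). Since 42 > 30, the longer storage is the one described as short.

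**The case against.** The strongest reply is that the arms are measured alike: same device, same wear period, remote collection throughout. A reader might infer from the contact counts that capture does differ by arm. The documents do not support that. They show unequal support for wearing and syncing, not unequal capture, and the planned 28-day gap fits within 30 days. Nothing ties syncing to data collections, and both arms are paid for each one completed. This stands, and the point is confined to what could happen.

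The listed content of the calls does not include a wear or sync check. That also stands: quick detection of non-wear in IS is plausible, not stated.

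Coaching is a named component of the intervention and the comparator is usual care, so unequal contact is the intended contrast. This is right. Steps gained because a coach encourages walking are effect; only the influence on wear and syncing is a measurement problem.

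Valid-day rules may sit in the full protocol or the analysis plan, neither of which is shown, so their absence is not held against the plan. This answers only part of the point. Such a rule can exclude unworn days, but it cannot recover overwritten ones or make wear equal. The contact pattern is a design matter that the article itself describes.

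A reader might also extend the point to WC wait against WC home intervention. The Statistical Analysis section specifies comparisons between groups at five time points up to week 14 and no contrast within WC, so that extension is not made.

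**Conclusion.** The point holds as a risk. In weeks 7-14 the primary-outcome device is part of coaching in one randomized arm only, with about 10 stated contacts in IS against 2 in WC and a longest planned gap of 7 days against 28. Unworn days counted as low steps would favour IS. The direction of bias from lost days is unknown.

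The contact count assumes one call in each of the 8 home weeks and no WC contact beyond what the article states. The 400 to 1200 steps/day are an illustration of scale under assumed wear and assumed zero-reading of unworn days. They should not be read as an estimate of bias in this trial.

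This is a cheap improvement to the design of a 16-participant pilot. It is worth making now because the trial is meant to inform a larger, remotely run one. The storage sentence is a separate error of rationale. It changes no result, and the visibility of steps to participant and coach still supports the choice of device.

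**What to change.** 1. Send the same automated wear, charge and sync reminder to both arms on the same weekly schedule from week 0 to week 14, continuing for WC to week 22. A weekly interval lies well inside the 30-day memory. A rule of syncing at least every 30 days would leave no margin.
2. Keep device-wear prompting out of the coaching calls. The coach's use of step data for coaching is unchanged.
3. Report valid wear days by arm beside the primary result, using whatever valid-day definition the analysis plan holds, applied without knowledge of arm.
4. Separately, correct the Aim 1 sentences on storage so that 30 days is not presented as ample and 42 days as short.

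The cost is an automated text or email and a few lines of protocol wording, with no added visits or staff. The downside is a light prompt to WC families, who would otherwise have none. Because both arms receive it equally, the coaching contrast is kept.

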### Measures

All measures for this study will attempt to be conducted remotely, when possible. There are a total of 5 data collection time points that will be compared between groups, which are baseline (week 0), posttransplant (~week 3), hospital discharge (~week 6), the middle of the home intervention or wait (week 10), and postintervention (after week 14). WC participants will undergo 2 additional measurements, a mid- (week 18) and postintervention measure (week 22) of their home intervention. The first data collection visit will occur in person, and participants will be guided through the measurement instruments. The remaining 4 data collections will be conducted through phone or videoconference. The rationale for doing so is to simulate a remotely conducted trial and thus allow for easier replication in a future multisite trial. In addition, research staff would not have to track down participants in various clinics throughout their treatment and outpatient rehabilitation phases.

#### Aim 1 (Primary Outcome): Physical Activity

Physical activity level will be measured by steps per day using a Fitbit Flex 2 wrist-worn tri-axial accelerometer. The participants from both the IS and WC groups will be equipped with the Fitbit Flex as soon as they join the study. IS participants will wear the Fitbit Flex and daily steps will be measured until they complete the entire study (hospital phase, weeks 0-6; home intervention phase, weeks 7-14). WC participants will wear the Fitbit Flex, and daily steps will be measured until they complete all 3 phases that are assigned to their group: hospital phase, weeks 0-6; home wait period, weeks 7-14; and home intervention, weeks 15-22. The Fitbit Flex has evidence to support good-to-excellent validity and reliability for measuring step counts across a variety of populations, both general [53] and clinical [54], and moderate data to support validity for pediatric patients with cancer [55]. Additional rationales for the Fitbit Flex include ease of use, robust memory (30 days), water resistance, the small size of the monitor unit, and low cost. Although Actigraph GT3x monitors have more evidence to support their use among pediatric patients with cancer and are considered the gold standard [55], we chose not to use them due to their short storage capacity (42 days max) and an inability for both the participant and the telecoach to view and monitor their steps (app and web-based feedback; a critical component of coaching). Step counts are inversely associated with mortality [56], as well as fatigue and cumulative symptoms among patients with pediatric cancer [57].

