### Statistical Analysis

Descriptive statistics, including means, SDs, and CIs, will be obtained for all study variables, and longitudinal smoothed scatterplots will be examined to identify temporal trends between groups, including the presence of potentially important nonlinear time trends. For aim 1 and aim 2 (measures of outcomes), outcomes will be modeled using all available measures, using mixed models with each participant included as a random effect to account for the repeated measures. Changes in means will be estimated with confidence intervals and compared between groups at 5 time points, which are baseline (week 0), posttransplant, hospital discharge (~week 6), midintervention or wait period (week 10), and postintervention (week 14) using estimated marginal means (also called least squares means). For aim 3, estimates with 95% CIs will be obtained for enrollment, dropout, and adverse event rates. Statistical tests will be 2-sided and will be performed using a significance level of *P*<.05. Statistical analyses will be performed using R (R Development Core Team) version 4.3.1 or higher (R Foundation for Statistical Computing).

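### Only the immediate-start arm plays controller-based boxing and rhythm games while wearing the wrist step counter in weeks 0-14, so error in the primary outcome can be tied to allocation

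*Protocol article*

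**What the plan says.** All references are to the protocol article.

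- **Outcome and sensor** (Aim 1, Primary Outcome: Physical Activity): "Physical activity level will be measured by steps per day using a Fitbit Flex 2 wrist-worn tri-axial accelerometer". The band is worn through every intervention week: "IS participants will wear the Fitbit Flex and daily steps will be measured until they complete the entire study". For IS this means weeks 0-14, and for WC weeks 0-22.
- **Intervention** (Supplies; ER Intervention): the equipment is a "Meta Quest 3 ER head-mounted display with handheld controllers, preinstalled with several active video games". "Exercise games will include boxing, fitness games, and rhythmic movement-to-music games". The hospital prescription is at least 15 minutes of exercise a day. At home it starts at three times per week, with a goal of 150 minutes per week by the fifth home week.
- **Contrast** (ER Intervention; Statistical Analysis): "WC participants will not receive the intervention until 8 weeks after hospital discharge". Outcomes are "compared between groups at 5 time points", the last being week 14.
- **Gaming time** (Aim 3: Intervention Acceptability): the headset's Move app logs active minutes per day. The article uses them only for attendance.
- **Device rationale** (Aim 1): the Fitbit is credited with "robust memory (30 days" of storage. The research-grade alternative is rejected "due to their short storage capacity (42 days max", and also because participant and telecoach cannot view steps on it.

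The validity evidence cited for the band concerns step counting in general, clinical and pediatric cancer populations. The article states no validation during controller-based play, no rule for play periods and no separate handling of steps logged during play.

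**The concern.** A wrist sensor has only wrist motion from which to infer steps. The exercise under test is largely repeated arm motion, some of it to a beat, and it was chosen for children who find prolonged walking or cycling hard. During the randomised comparison that motion is prescribed in IS and absent in WC.

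Randomisation, a blinded assessor and a larger sample do not remove error of this kind, because it arises after allocation and follows the treatment. The mixed model would carry it into the group contrasts at the time points after baseline.

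The interpretation of Aim 1 is at stake. The article justifies steps by their association with mortality, fatigue and symptoms, and home coaching aims to promote walking and community activity. Swings or punches counted as steps are none of these. A step gain that arose only during play would show mainly that the games were delivered, which Move minutes already show directly, and it could be carried into the planning of the larger trial.

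**Working it through.** The article gives no effect size, SD or power figure for steps, so there is nothing to reproduce. The check has three parts.

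**1. Is exposure to the possible error tied to the arm?**

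| Period | IS | WC |
|---|---|---|
| Weeks 0-6, hospital | band on, games prescribed daily | band on, no games |
| Weeks 7-14, home | band on, games prescribed | band on, no games |
| Weeks 15-22, home | finished | band on, games prescribed |

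Yes. Within the between-group comparison only IS is exposed. In weeks 15-22 WC becomes exposed, which affects its change from wait to intervention.

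**2. How large could it be?** False steps/day = gaming minutes/day × false steps per gaming minute. Minutes come from the ER Intervention section and assume full adherence. The rate is an assumption, because the documents give none.

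- Hospital: 15 min/day.
- Home start, reading the prescription as 3 × 15 = 45 min/week: 45/7 = 6.43 min/day.
- Home goal: 150/7 = 21.43 min/day.

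| Assumed rate per minute | Hospital | Home start | Home goal |
|---|---|---|---|
| 0 | 0 | 0 | 0 |
| 10 | 150 | 64 | 214 |
| 30 | 450 | 193 | 643 |
| 60 | 900 | 386 | 1,286 |
| 100 | 1,500 | 643 | 2,143 |

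As an illustration of the consequence, take a two-sample t test at one time point with 8 per arm, two-sided 5%, 14 degrees of freedom and no true difference. The noncentrality is bias / (SD × √(2/8)) = bias / (0.5 × SD). For a bias of 1,286 and an SD of 2,000 it is 1.286. The chance of P<.05 at the home goal is then:

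| Assumed between-child SD (steps/day) | Rate 10 | Rate 30 | Rate 60 |
|---|---|---|---|
| 1,000 | 7% | 22% | 67% |
| 2,000 | 5.5% | 9% | 22% |
| 3,000 | 5% | 7% | 13% |

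The SDs are also assumptions. The range runs from no visible harm to serious harm, and nothing in the article narrows it.

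**3. Storage rationale.** The article calls 30 days robust and 42 days short, although 30 < 42. The hospital phase alone is about 6 × 7 = 42 days. Scheduled contacts at about weeks 0, 3, 6, 10, 14, 18 and 22 leave gaps of 21, 21, 28, 28, 28 and 28 days. All are inside 30 days if a sync is made at each contact.

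**The case against.** **Size and direction are not documented.** No false-step rate, step algorithm or usual step count is given. The rate could be near zero. The error could also run the other way, if arm exercise without stepping is under-counted. This stands: the tables above are scenarios, and a reader should not infer that an observed step difference would be artefact.

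**Not every IS day involves play.** Home play starts at three times per week, so 7 − 3 = 4 days a week have no prescribed session at that stage, and adherence may be incomplete. This stands too. A reader might infer that the whole IS step record is contaminated, and the ER Intervention section does not support that.

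**Gaming is physical activity.** Aim 1 concerns physical activity participation, not walking alone, so movement during play is not irrelevant to it. This stands, and it counts against replacing the primary outcome with steps outside play, which would remove the prescribed exercise from the outcome. Taking the band off for play would create non-wear linked to IS. It does not justify reading a step difference as more ambulation.

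**This is a condensed article on a 16-child pilot.** Wear instructions and step processing may be in a fuller document, and the article says that larger studies must confirm its results. That lowers the urgency. But the outcome, sensor site, wear period and games are all stated here, and the conflict lies in how they combine.

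**The device choice does not depend on storage.** The app and web feedback reason stands alone, so the storage wording is a minor matter.

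**Conclusion.** The point holds in limited form. As written, the plan permits step-count error linked to allocation in the week 0-14 comparison, and the same error in the WC wait-to-intervention change in weeks 15-22. The article does not address it.

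The size and direction are unknown. Assumed rates of 10-100 false steps per gaming minute at full adherence give about 150-1,500 steps/day in hospital, 64-643 at home start and 214-2,143 at the home goal; a rate of zero gives none. These figures rest on the assumed rates and on reading the home start as 45 min/week.

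The documents do not show that Aim 1 is invalid or that total steps must be abandoned. They do show that a step difference alone cannot be read as more walking. The 30-day versus 42-day wording is a real but minor inconsistency.

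**What to change.** 1. Keep total daily steps as the primary outcome and keep the band on during play.
2. Record start and stop times of play, from the headset log if it holds them and otherwise in a one-line diary. The article documents only daily Move totals, so session times should be captured prospectively.
3. Pre-specify a key sensitivity analysis of daily steps excluding play time, using time-stamped step data if they can be retrieved and otherwise comparing non-play days. Apply the same rule to WC weeks 15-22.
4. Report Move active minutes beside the step result. State in advance that an IS-WC step difference will not be read as more walking unless it persists outside play.
5. Correct the storage rationale, rest the device choice on app and web feedback, and confirm a sync in both arms at each scheduled contact.

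The cost is a small diary burden, one added analysis and some wording. The sensitivity analysis leaves out real steps taken during play. The non-play-day fallback is weak in hospital, where play is prescribed daily and days without it may be days when the child is unwell, so time-stamped data are preferable.
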